## Abstract

**Background:**

The worldwide rise in the prevalence of noncommunicable diseases has increased the recognition of the need to identify modifiable risk factors for preventing and managing these diseases. The office worker, as a representative group of physically inactive workers, is exposed to risk factors for metabolic syndrome, which is a primary driver of noncommunicable diseases. The use of virtual reality (VR) exergames may offer a potential solution to the problem of increasing noncommunicable disease prevalence, as it can help individuals increase their physical activity levels while providing a more immersive experience.

**Objective:**

This exploratory study aims to examine the interventional efficacy of at-home immersive VR exergames on metabolic syndrome biomarkers among office workers. Additionally, it seeks to investigate the impacts of at-home immersive VR exergames on the active and sedentary behaviors of office workers.

**Methods:**

A 3-arm, single-blinded pilot randomized controlled trial will be conducted to examine the therapeutic effects of at-home immersive VR exergames. A total of 120 Chinese office workers, engaging in less than 150 minutes per week of moderate to vigorous intensity physical activity, will be recruited via a convenience sampling method. The participants, who will be tested over a 12-week period, will be randomly assigned to one of three groups: (1) the VR exergame intervention group, (2) the regular physical activity control group, and (3) the nonexercise control group. Throughout the 12-week trial, three categories of variables will be collected across the three groups: clinical risk factors associated with metabolic syndrome, active and sedentary behaviors, and demographics. To analyze variance among the groups, a mixed linear model will be applied to assess the efficacy of each group. Differences in metabolic syndrome clinical risk factors among all groups will be used to evaluate the effects of at-home immersive VR exergames. Changes in active and sedentary behaviors will also be used to determine the impacts of VR exergames on metabolic syndrome.

**Results:**

The ethics committee of Guangzhou University, China, approved this study on September 25, 2024. Participant recruitment will begin in early 2025 and continue for approximately 3 months. Data will be analyzed after the 12-week trial is completed, with full results expected to be presented in early 2026.

**Conclusions:**

This study explores an emerging topic by applying an at-home immersive VR exergame intervention, potentially contributing to understanding the effects of an exergame program on metabolic syndrome risk among office workers.

**Trial Registration:**

ClinicalTrials.gov NCT06556784; https://clinicaltrials.gov/study/NCT06556784

**International Registered Report Identifier (IRRID):**

PRR1-10.2196/64560

## Introduction

Noncommunicable diseases, such as cancer, cardiovascular diseases, diabetes, and heart disease, constitute the foremost cause of death internationally [1]. Noncommunicable diseases accounted for 63% or 36 million global deaths in 2008, which increased to 74% in 2019 [2,3]. The increasing prevalence of noncommunicable disease deaths worldwide has increased the need to identify modifiable risks in preventing and managing these diseases.

Metabolic syndrome is a common chronic disease characterized by the co-occurrence of several major biomarkers, including high-density lipoprotein cholesterol (HDL-C), low-density lipoprotein cholesterol (LDL-C), impaired fasting glucose, insulin, triglycerides, blood pressure, waist circumference, and BMI [4,5]. Moreover, as a route to many noncommunicable diseases, such as cancer, cardiovascular diseases, and type 2 diabetes [6-8], metabolic syndrome plays a pivotal role in health status. For example, several systematic reviews have shown that individuals with metabolic syndrome are approximately two to five times more susceptible to developing cardiovascular disease and type 2 diabetes [9-11]. Although metabolic syndrome is one of the threats to a healthy life [12], its prevalence is increasing globally [13]. For example, a study conducted in the United States reported an increase of more than 35% in the prevalence of metabolic syndrome among US adults from 1988-1994 to 2007-2012 [14]. A systematic review reported that approximately 20% of the adult population in most Asian Pacific countries is struggling with a metabolic syndrome epidemic [15]. However, as an effective approach to mitigate the risk and treatment of metabolic syndrome, physical activity is facing a worrisome status across all countries [16,17].

Employed adults, the largest population in the world, spend a large portion of their waking time in the workplace [18,19]. Especially in desk-based workplaces, most of this time is spent sitting [20-22]. For example, in desk-based workplaces, Japanese workers spend approximately 70% of their time sitting with a low level of physical activity [23]. With the ongoing advancement of technology, the worldwide phenomenon of physical inactivity among employed adults has been occurring increasingly in recent decades [24]. An example study conducted in China revealed that the energy expenditure of occupational activity decreased by more than 22% and that the energy expenditure of domestic activity decreased by more than 51% over 9 years [25]. Other studies in the United States reported a steadily increasing trend of low-activity occupations of 76% from 1950 to 2000 [26] and a decreasing occupation-related caloric expenditure of more than 124 calories per day from 1960 to 2008 [27]. Prolonged sitting time adversely affects cardiometabolic health among office workers, an already at-risk population for metabolic syndrome [28]. For example, a study conducted in Central Iran reported that approximately 36% of office workers had metabolic syndrome [29]. Other studies have revealed that approximately one in ten office workers are at risk of metabolic syndrome in Korea [30] and Great Britain [31]. Physical activity promotion interventions have a strong positive impact on people with metabolic syndrome [32]. Nevertheless, several factors, such as the nature of the job and lack of motivation and time [33-35] for exercise, remain key barriers for office workers to adhere to an active lifestyle. Consequently, gym attendance rates are low even among people paying for membership [36], and more than 75% of people fail to keep their health target for more than 3 years [37].

Exergames are defined as video games that require players to be physically engaged in them to play [38,39]. Several systematic and narrative reviews have provided preliminary evidence for the correlations between playing exergames and users’ physical activities [40,41]. For example, the contribution of exergames to increasing older adults’ health and wellness through physical activity has been validated [41]. Previous studies have demonstrated that exergames can be used as interventions to increase physical activity, particularly among obese individuals [42]. With the ongoing advancement of virtual reality (VR) technology, exergames have become more immersive for users. The concept of immersion is defined as “users’ engagement with a VR system that results in being in a flow state” [43]. Owing to the technology limitations of conventional VR, several shortages have been presented to users, such as difficulty in producing dynamic natural environments and interaction deficiencies in human-environment simulations. In contrast, with the development of visualizations and interactions with virtual environments, new immersive VR methods can address these limitations and lead to more accurate and efficient virtual environment assessments [44]. Additionally, its new application in exergame areas has already shown potential for promoting the health and well-being of some disabled youth [45]. Nevertheless, research on the health impact of immersive exergames remains rare. A search of the terms “immersive exergame” or “video game,” “physical activity” or “exercise,” “cardiometabolic” or “metabolic syndrome,” and “office worker” produced 0 results in the Scopus database as of May 6, 2024 [46]. Thus, using immersive exergames to promote physical activity in relation to cardiometabolic health is still in its infancy among office workers, with a need for increased knowledge about this topic. Therefore, as the first randomized controlled trial (RCT), to the best of our knowledge, the purpose of this study is to examine the effects of at-home immersive VR exergames on clinical risk factors among office workers, an already at-risk population for metabolic syndrome.

## Methods

### Study Design

RCTs, a top-level research methodology in the area of evidence-based medicine [47], have played a significant role in evaluating the effects of lifestyle changes on metabolic syndrome [48-50]. This protocol is a longitudinal pilot study that uses a 3-arm parallel-group RCT to examine the interventional efficacy of an at-home immersive VR exergame on several clinical risk factors of metabolic syndrome among office workers. On the basis of prior research on exercise and physical activity interventions [48,51], a 12-week duration was selected for this trial, as it is a commonly used period for evaluating the efficacy of interventions targeting metabolic syndrome. Several clinical risk factors for metabolic syndrome, as well as active and sedentary behavior, will be monitored in three stages during this 12-week trial. Stage 1 will be at the start of the trial, Stage 2 at week 6, and Stage 3 at the end of the trial. The therapeutic effects of the at-home immersive VR exergame intervention for metabolic syndrome will be evaluated by comparing these risk factors among three groups: the VR exergame intervention group, the regular physical activity control group, and the nonexercise control group. The study follows two checklists: the CONSORT-EHEALTH (Consolidated Standards of Reporting Trials Statement for Randomized Controlled Trials of Electronic and Mobile Health Applications and Online TeleHealth) [52] and the SPIRIT (Standard Protocol Items: Recommendations for Interventional Trials; Multimedia Appendices 1 and 2) [53,54].

### Participant Recruitment

For this exploratory study, a convenience sampling method will be used to recruit 120 office workers from six office-oriented information technology companies in Guangzhou City, Guangdong Province, located in Southern China. This group represents a high proportion of physically inactive individuals [55,56] and is at greater risk of developing metabolic syndrome [56-58]. Recruitment emails will be sent to participants via the Tencent Enterprise Mailbox [59], a platform that allows companies to create email accounts with their corporate domain. This platform serves as a communication and office tool to support enterprises in providing unified notifications to office workers and to support office workers in providing timely and efficient feedback. The inclusion criteria for participants are office workers who are 16-60 years old (based on the standard age of the Labor Law of the People’s Republic of China), capable of standing and exercising, and have no history of heart disease, cancer, or dementia. Additionally, participants should be interested in playing with the exergames and willing to adhere to a 12-week intervention exergame treatment because of the nature of the trial.

This research aims to examine the effects of at-home immersive VR exergames on the clinical risk factors for metabolic syndrome. Hence, individuals who are already engaged in more than 150 minutes per week of moderate to vigorous intensity physical activity will be excluded [60]. Additionally, pharmacological treatments, such as metabolic syndrome–related medicines (insulin sensitizers and biguanides, orlistat, sibutramine, etc), some surgeries (bariatric surgery), and traditional Chinese medicine (herbal medicine of ginseng, berberine, bitter melon, etc), are the other exclusion criteria because of their potential to influence cardiometabolic outcomes [61,62].

First, to encourage participation, some basic information related to exercise for health and immersive VR exergames will be introduced to potential participants. After a detailed explanation of what is needed during the trial, a precheck of the inclusion and exclusion criteria will be asked to identify eligible participants. Then, participants who meet the criteria will be instructed to review the information and provide informed consent and assent for this study. Given the nature of the clinical risk factors to be collected, a data collection center will be arranged at a cooperative clinic, and its address will be shared with all the participants for data collection and allocation of experimental equipment and material at the start of the trial.

### Intervention and Control Groups

Following RCT guidelines [63,64], participants will be randomized into three equal groups: (1) the at-home immersive VR exergame intervention group, (2) the regular physical activity control group, and (3) the nonexercise control group. Including both the regular physical activity and nonexercise control groups will help determine whether VR exergame intervention offers unique benefits beyond those achieved through traditional exercise or no intervention. This design allows us to isolate the specific effects of immersive VR exergames. The at-home immersive VR exergame intervention includes a 12-week trial of exercise using Meta Quest 2, as shown in Figure 1. The Meta Quest 2 device is a valid tool that has been used in previous studies to support physical activity [65-68]. A VR headset and 2 handheld controllers are contained in the Meta Quest 2 set. Several active aerobic game apps will be installed on headset devices. These apps include the following [69]: Beat Saber (exercise: full-body, aerobic), Synth Riders (exercise: dance, aerobic), OhShape (exercise: dance, aerobic), Ragnarock (exercise: arms, shoulders, aerobic), Dance Central (exercise: dance, aerobic), Until You Fall (exercise: back, shoulders, arms, aerobic), In Death: Unchained (exercise: arms and shoulders, endurance/aerobic), and Space Pirate Trainer (exercise: full-body, aerobic). In these immersive games, the users can present their body movements in the game world from a first-person perspective. Moreover, they are all designed to motivate users to participate in physical movements with various categories of motivational affordances. For example, Beat Saber is a rhythm game in which users need to move their bodies to slice blocks at an exact angle. Physical activities such as arm waving, moving, and squatting with an accelerating speed are motivated in the game with affordances of rank, point, and record. The participants in the VR exergame intervention group will be instructed to play one or more of these exergames for at least 150 minutes per week, which is in line with the World Health Organization’s physical activity guidelines [60]. They will be requested to record the frequency and duration of their exergaming sessions. Participants in the regular physical activity control group will engage in a physical activity routine similar in duration and intensity to the VR exergame intervention. Participants in the nonexercise control group will not receive any specific exercise instructions. All groups will be advised to maintain regular eating and working habits without making significant changes throughout the 12-week trial. After completing the trial, participants in both control groups will be offered the same procedures as the intervention group, but their data will not be collected.

**Figure 1 figure1:**
[figure not shown]
An example of exercising with aerobic immersive VR exergame using Meta Quest 2 (source: the authors). VR: virtual reality.

### Measures

This exploratory pilot study aims to test the intervention of at-home immersive VR exergame on metabolic syndrome. Two variables, including clinical risk factors for metabolic syndrome and active and sedentary behaviors, will be measured throughout the three stages of the trial. Demographic information will be collected only at stage 1. Major clinical risk factors are objectively measured from participants’ blood tests and a sphygmomanometer. The Global Physical Activity Questionnaire (GPAQ) will be used to measure participants’ active and sedentary behaviors. A summary of the stages, measures, and indicators is shown in Table 1.

**Table 1 table1:** Summary of stages, measures, and indicators.

Measures and indicators		Timeline		
		Stage 1	Stage 2	Stage 3
**Demographics**				
	Age, gender	✓		
**Clinical risk factors**				
	HDL-C^a^	✓	✓	✓
	LDL-C^b^	✓	✓	✓
	Impaired fasting glucose	✓	✓	✓
	Insulin	✓	✓	✓
	Triglycerides	✓	✓	✓
	Blood pressure	✓	✓	✓
	Waist circumference	✓	✓	✓
	BMI	✓	✓	✓
**Active and sedentary behaviors**				
	Exercise time (including exergaming time)	✓	✓	✓
	Sedentary time	✓	✓	✓

^a^HDL-C: high-density lipoprotein cholesterol.

^b^LDL-C: low-density lipoprotein cholesterol.

To test the therapeutic effect of this intervention, primary clinical risk factors for metabolic syndrome, including blood tests for HDL-C, LDL-C, impaired fasting glucose, insulin, and triglycerides, along with sphygmomanometry of blood pressure, waist circumference, and BMI, will be measured [4,70,71]. Owing to several merits of immersive VR exergames, such as physical engagement [38,39], the nature of immersion, and attractiveness [43], the use of VR exergames may have a significant effect on behaviors, such as exercise and sitting time [72]. Therefore, we use the GPAQ to observe the changes in active and sedentary behaviors produced by immersive VR exergames. Moreover, the validity of the GPAQ has been proven for monitoring physical activity in health promotion research [73]. The whole questionnaire includes 16 items for 3 intensities (light, moderate, and vigorous intensity) of physical activity and sedentary behavior during work, transport, and leisure time [74]. The paper form will be printed and passed to participants to assess the changes in active and sedentary behaviors during the trial.

### Study Procedure

Each group in this study will consist of 40 randomly allocated participants (using a simple computer-generated random number sequence managed by JZ), and the trial will be conducted in a single-blinded structure. In this three-arm study, participants will receive the VR exergame intervention, regular physical activity, or no exercise at all. The participants will inherently be aware of their assigned activity. However, they will be blinded to the specific study hypotheses and the detailed objectives regarding comparing the 3 groups. To reduce perceived differences, participants in both control groups will receive VR exergame devices after completing the trial, but no data will be collected from this phase. Additionally, outcome assessors and data analysts will remain blinded to group assignments to prevent bias in data collection and analysis. This single-blind design helps reduce bias in the interpretation of the study results, even though participants are aware of their assigned activity.

The comprehensive framework for this protocol consists of 3 stages over 12 weeks and the allocation of items for each stage is shown in Table 2. In stage 1, when participants arrive at the data collection center, experiment coordinators will distribute and explain the manual booklet to all participants, which includes a description of the procedures, requirements, and address for inquiries. After participants have confirmed the contents and requirements of the manual, the experiment coordinators and clinic nurses will collect demographics, clinical risk factors, and GPAQ from all participants as the baseline data. A Meta Quest 2 set of equipment (entire trial), GPAQ questionnaire (0 to 6 weeks), and a recording sheet of exergaming time (0 to 6 weeks) will be additionally assigned to the VR exergame intervention group. In stage 2, the GPAQ questionnaire (7 to 12 weeks) will be assigned to all 3 groups and a recording sheet of exergaming time (7 to 12 weeks) will be additionally assigned to the VR exergame intervention group. In stage 3, only the Meta Quest 2 set of equipment will be assigned to both control groups. The necessary items for each stage will be passed to participants when they arrive at the data collection center.

**Table 2 table2:** Timeline and allocation of items.

	Stage 1^a^	Stage 2^b^	Stage 3^c^
VR^d^ exergame intervention group	Manual booklet Demographic questionnaire GPAQ^e^ Meta Quest 2 set Recording sheet of exergaming time	GPAQ Recording sheet of exergaming time	—^f^
Regular physical activity control group	Manual booklet Demographic questionnaire GPAQ	GPAQ	Meta Quest 2 set
Nonexercise control group	Manual booklet Demographic questionnaire GPAQ	GPAQ	Meta Quest 2 set

^a^Start of the trial.

^b^Week 6 of the trial.

^c^End of the trial.

^d^VR: virtual reality.

^e^GPAQ: Global Physical Activity Questionnaire.

^f^Not applicable.

All participants will be asked to visit the data collection center in three stages for data collection and experimental material allocation. The self-reported GPAQ questionnaire will be completed by all participants at home, as it is a convenient at-home format for exploring impacts on active and sedentary behavior. The VR exergame intervention group will record the frequency and duration of their exergaming sessions, the regular physical activity control group will track their daily exercise routines, and the nonexercise control group will report any physical activities they perform beyond their baseline. Participants will be asked to bring all self-report sheets to the data collection center at stages 2 and 3. Coordinators will collect and summarize all the completed questionnaires and recording sheets for data processing. Major clinical risk factors are objectively measured from participants’ metabolic syndrome biomarkers, which are operated by professional nurses at the data collection center (cooperative clinic). Since there is a fasting biomarker for testing metabolic syndrome, all participants are required not to consume any food or drink 12 hours before blood sample collection in the morning. After the major clinical risk factor data from all the participants for the entire trial are collected, the experiment coordinators will visit and obtain the data from the data collection center.

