### Ethical Considerations

This study was approved by the Institutional Ethics Committee of Guangzhou University, China (2024-112; September 25, 2024). Initially, potential participants will be provided with basic information regarding the benefits of exercise for health and immersive VR exergames. Subsequently, interested individuals will receive a detailed explanation of the study process, and they will be asked to sign the informed consent and assent forms. In addition, some personal information is required during this trial, including name, age, gender, email address, home address, and phone number for the purpose of marking data, sending the results of blood tests and diagnosis of metabolic syndrome, or analyses (eg, as covariates). All participant information will be collected directly by the experiment coordinator (JZ) to ensure the privacy of their personal information. Strict measures will be implemented to manage and store all the collected data. To compensate for participation, participants will be rewarded with RMB 150 (approximately US $21) for completing each stage, whereas participants who complete all the processes of the trial will be rewarded with RMB 500 (approximately US $71). All incentives will be sent via a registered postal cash envelope. For visiting the data collection center at each stage, transportation fees will also be reimbursed.

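### The randomisation sequence sits with a coordinator in participant contact, and the blanket assessor-blinding statement cannot cover coordinators; for nurse-read waist and blood pressure, blinding is left unprotected rather than shown to fail

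*Protocol article*

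**What the plan says.** All under Study Procedure in the protocol article unless noted.

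- **Blinding.** Participants know their activity. The stated safeguard is that "outcome assessors and data analysts will remain blinded to group assignments to prevent bias in data collection and analysis". The roles that count as outcome assessors are not listed.
- **Sequence.** Allocation to three groups of 40 is done "using a simple computer-generated random number sequence managed by" one team member, identified by initials. Under Ethical Considerations the same initials belong to the coordinator: "All participant information will be collected directly by the experiment coordinator".
- **Baseline.** At stage 1, "the experiment coordinators and clinic nurses will collect demographics, clinical risk factors, and GPAQ from all participants as the baseline data".
- **Sheets.** At stage 2, "a recording sheet of exergaming time (7 to 12 weeks) will be additionally assigned to the VR exergame intervention group". The regular-activity arm tracks its exercise routine, and the nonexercise arm reports activity beyond baseline. Participants bring their sheets to the centre at stages 2 and 3. There, "Coordinators will collect and summarize all the completed questionnaires and recording sheets for data processing".
- **Hand-over.** "The necessary items for each stage will be passed to participants when they arrive at the data collection center". Table 2 gives a headset to the VR arm at stage 1 and to the two control arms only at stage 3.
- **Clinical measurements.** Professional nurses take these at the cooperating clinic. Coordinators obtain the clinical data only once the whole trial's measurements are complete.

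**The concern.** Two safeguards are in question.

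The first is concealment. A person who holds the sequence and also deals with participants can know the next assignment before a volunteer is committed. Participant Recruitment requires volunteers to be interested in exergames, so there is a plausible motive to steer some of them. With group sizes fixed at 40, a list holder can also work out the remaining assignments towards the end.

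The second is blinded assessment. Because participants cannot be blinded, the protocol relies on blinded assessors and analysts to limit bias. Waist circumference and sphygmomanometer pressure are both among the primary clinical risk factors, and both depend on the person taking the reading. If that person has just seen a headset or an exergaming sheet, the reading can drift with expectation. Under Analyses, the pilot's effect estimates are to inform a larger trial, so such a bias would carry forward.

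**Working it through.** The point rests mainly on comparing role assignments. The protocol has no figure here to reproduce.

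**Step 1: sequence holder and participant contact.** Study Procedure and Ethical Considerations show the same initials, so one person manages the sequence and is the experiment coordinator. Study Procedure also has "experiment coordinators will distribute and explain the manual booklet to all participants", so the coordinator role involves meeting participants at stage 1. No text separates sequence-holding from contact or says when an assignment is released. Concealment is not secured as described.

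**Step 2: coordinators and the blinding statement.** Coordinators collect and summarise the GPAQ, a source of outcome data, along with the recording sheets. Only the VR arm has an exergaming sheet, and the other two arms record different things. Anyone handling these sheets can tell the arm. If coordinators count as outcome assessors for the behavioural outcomes, the unqualified statement is contradicted. If they do not, the protocol should say so.

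**Step 3: nurses and the primary clinical outcomes.** No text says that nurses see the allocation or handle items. Yet the exposure is there at each stage:

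| Stage | Arm-revealing items at the clinic visit |
|---|---|
| 1 | Headset and exergaming sheet issued to the VR arm |
| 2 | Arm-specific sheets brought in; new exergaming sheet issued to the VR arm |
| 3 | Arm-specific sheets brought in; headsets issued to control arms only |

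Items are passed over on arrival, and only at stage 1 does the narrative place data collection before the equipment sentence. For stages 2 and 3, nothing puts measurement first.

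**Step 4: which outcomes are exposed.** Of the eight listed clinical indicators, blood pressure and waist circumference are the ones most open to operator influence. The five blood tests (HDL-C, LDL-C, glucose, insulin, triglycerides) are little affected. The GPAQ is completed at home by participants who know their arm, so assessor blinding could not protect it.

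**Step 5: illustrative size.** Input from the protocol: 40 per arm. Assumed: an arm-differential reading bias b, in SD units, at one time point. The documents give no value for b.

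- SE of a between-arm difference = sqrt(2/40) = 0.224 SD.
- Shift = b / 0.224. Rejection rate under no true effect = P(Z > 1.96 − shift) + P(Z < −1.96 − shift).

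| Assumed b (SD) | Shift (SE) | Rejection rate |
|---|---|---|
| 0.1 | 0.45 | 0.065 + 0.008 = 0.073 |
| 0.2 | 0.89 | 0.143 + 0.002 = 0.145 |
| 0.3 | 1.34 | 0.268 + 0.001 = 0.269 |

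The planned analysis is a mixed model over three stages, so these figures show only the order of magnitude.

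**The case against.** The strongest reply is that the protocol names nurses as the assessors of the primary outcomes and keeps the clinical data from coordinators until the trial's measurements are complete. That stands. A reader might infer that assessor blinding fails for waist and blood pressure, or that the trial has a 15% false-positive rate. The documents support neither. The sentence naming coordinators alongside nurses for clinical risk factors concerns baseline only, and it can be read as nurses measuring while coordinators handle forms.

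A reader might also infer that coordinators hand out the headsets. The text there is passive and names coordinators only for the booklet, which goes to everyone. Hand-out by coordinators is plausible but not stated.

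On concealment, the sentence about collecting participant information sits in a privacy context and does not say that this coordinator screens, enrols or assigns. If the whole cohort were enrolled before any allocation, foreknowledge could not steer enrolment. So a breach is not shown.

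It is also fair that an article may leave the concealment mechanism to a fuller protocol. That does not dispose of the point, which rests on what the article states: one person in both roles, coordinators handling arm-specific sheets, and a blinding claim without limits.

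Finally, where coordinators do see the arm, the main data affected are self-reports that blinding could not rescue, and the article already lists self-report as a limitation. That limits the consequence for behavioural outcomes. It does not make the statement accurate.

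**Conclusion.** The point holds in three parts of different strength.

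1. **Concealment is not secured as described.** The dual role is documented. That it was or would be used to steer enrolment is not.
2. **The blinding statement cannot cover coordinators.** This follows from the text and calls for a correction of wording.
3. **Nurse-read waist and blood pressure are exposed, but no failure is shown.** The exposure depends on whether nurses see the items before measuring, which the article does not settle.

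The size of any bias is unknown. The range of about 7% to 27% for a nominal 5% test assumes an arm-differential bias of 0.1 to 0.3 SD, at a single time point, with 40 per arm. It shows why the order of tasks matters and is not an estimate for this trial. The matter should be put right, and is best settled before enrolment because it is inexpensive to do so.

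**What to change.** - Have the sequence held by a team member with no participant contact, or in sealed opaque envelopes.
- Release each assignment only after consent, eligibility and all stage 1 measurements are recorded.
- At every stage, have nurses complete all clinical measurements before any headset or sheet is handed over or collected. Coordinators then deal with equipment and sheets and take no clinical measurement.
- Limit the blinding statement to the nurses, the laboratory and an analyst who receives arms as codes. State that coordinators are not blinded and that the GPAQ is self-reported by participants who know their arm.

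**Cost.** Minor reassignment of tasks and re-ordering of the visit, with no extra visits or participants. The article does not show whether an existing team member is free of participant contact. If none is, envelopes are a small added procedure.
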